#### Analyses of cost-effectiveness and quality of life data

Overall analysis will be performed from the perspective of the health care system; basic information will also be collected on employment status during follow-up from the annual Health Service Resource use questionnaire. Unit costs obtained from centres and from national sources will be used to obtain a cost per patient. Missing data will be handled via multiple imputations in statistical analyses.

In line with the primary outcome of the trial, the main outcome measure in the cost-effectiveness analysis will be life years gained. These will be estimated within-trial and over the patients' lifetime, by taking the sum of life years obtained in each arm of the trial within the follow-up period and modelling subsequent life expectancy, using different assumptions about any within-trial treatment effects continuing. The cost per quality adjusted life year (QALY) will be calculated in the same way, using results from the EQ-5D annual questionnaires.

The cost-effectiveness analysis will be reported in terms of the incremental cost per life year and the incremental cost per QALY gained. All resource use, cost, outcome and cost-effectiveness information will be reported as the mean per patient in each arm of the trial and the mean difference, with appropriate measures of variance. Cost-effectiveness in sub-groups will be estimated by applying any overall relative risk reduction and cost reduction to different baseline absolute risk groups. Cost-effectiveness acceptability curves and net benefit statistics will also be reported.

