### Follow-up

A summary of the follow up is shown in Table 1.

**Table 1 T1:** Follow-up schedule

	**Pre-op**	**Intra-op**	**Pre-discharge**	**6 wk clinic visit (± 1 m)**	**Annual telephone and postal follow up for 10 years (± 1 m)**
***Baseline characteristics***	***√ ***				
***Clinical history***	***√ ***				
***Physical exam***	***√ ***			***√ ***	
***Medications***	***√ ***		***√ ***	***√ ***	***√ ***
***LV function assessment***	***√ ***				
***Quality of Life assessment ***	***√ ***				***√ ***
***Health Service Resource use***		***√ ***	***√ ***	***√ ***	***√ ***
***Operation details***		***√ ***			
***Clinical Outcomes***			***√ ***	***√ ***	***√ ***

Annual Quality of Life questionnaires (Table 2) will be sent to study participants by post, no clinic visits are required apart from the routine clinical 6-week post operative visit. Participants will be sent stamped addressed envelopes to improve the return rates of postal questionnaires. Study co-ordinators will telephone participants to alert them to the questionnaires arrival and to ask them about medications, adverse events and health services resource use.

**Table 2 T2:** Quality of Life questionnaires

**Questionnaire**	**Information collected**	**YEAR**										
		
		Pre-op	1	2	3	4	5	6	7	8	9	10
Rose (shortened form)	Simple, evaluates angina	+	+	+	+	+	+	+	+	+	+	+
EuroQuol-5D	Short and simple, for economic evaluation	+	+	+	+	+	+	+	+	+	+	+
SF-36	Detailed, examines eight separate dimensions	+					+					+

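### The QALY difference, as described, makes no use of the pre-operative EQ-5D, so the cost per QALY is somewhat less precise than the collected data allow

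*Protocol article*

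**What the plan says.** All of this comes from the protocol article.

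- **Main economic outcome.** Under Analyses of cost-effectiveness and quality of life data, "the main outcome measure in the cost-effectiveness analysis will be life years gained". Within the trial these are obtained "by taking the sum of life years obtained in each arm of the trial within the follow-up period", with later life expectancy modelled.
- **QALYs.** The same section then says: "The cost per quality adjusted life year (QALY) will be calculated in the same way, using results from the EQ-5D annual questionnaires".
- **Reporting.** The results paragraph states that "cost-effectiveness information will be reported as the mean per patient in each arm of the trial and the mean difference", "with appropriate measures of variance". It does not call the difference adjusted or unadjusted.
- **Baseline score.** Table 2, under Follow-up, schedules EQ-5D pre-operatively and in each of years 1 to 10, and describes its purpose as "Short and simple, for economic evaluation".
- **Covariates.** The only mention of prognostic variables is under Type of analyses. It is tentative and concerns time-to-event data.

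**The concern.** A sum per arm, then a mean per arm and a difference, suits life years, because a life year has no baseline value. A QALY is different. The pre-operative utility predicts later utility and, if the first-year area under the curve starts from it, also enters the QALY directly. The article carries the life-year method over to QALYs and leaves the baseline score unused.

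Two things follow. Any chance difference between the arms in baseline utility passes in part into incremental QALYs. The interval for incremental QALYs is also wider than it need be. Incremental QALYs are the denominator of the cost per QALY and enter the net benefit and acceptability curves. The gain to be expected over ten years is small, so a modest shift in the denominator is visible in the ratio.

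**Working it through.** **The plan's own figure.** The only sample size in the article is for mortality: 25% v 20% at 10 years, 90% power, 5% alpha, 2928 patients. With pooled variance and a two-sided test:

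n per arm = [1.960 × √(2 × 0.225 × 0.775) + 1.2816 × √(0.25 × 0.75 + 0.20 × 0.80)]² / 0.05² = (1.1575 + 0.7555)² / 0.0025, which rounds up to 1464.

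The total is 2928, so the figure reproduces exactly. Nothing below alters it. The article gives no figure for quality of life or QALYs.

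**Inputs**
- From the article: 25% v 20% mortality; 1500 per arm.
- Assumed, because the article gives none: baseline EQ-5D SD 0.20 to 0.30; mean later utility 0.75; SD of 10-year QALYs about 2.5; correlation ρ between baseline EQ-5D and 10-year QALYs 0.2 to 0.44. The SD and ρ come from simulation with baseline SD 0.20 to 0.25, later utility SD 0.15 to 0.20, baseline-to-later correlation 0.3 to 0.7 and 25% mortality.

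**Step 1: the QALY gain implied by the planned effect.** With exponential survival, mean life years to 10 years are (1 − S)/λ, where λ = −ln(S)/10.
- S = 0.75: 0.25/0.02877 = 8.690
- S = 0.80: 0.20/0.02231 = 8.963
- Difference: 0.273 life years; × 0.75 = 0.205 QALYs (0.19 to 0.22 at utility 0.7 to 0.8)

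This assumes equal utility in both arms.

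**Step 2: precision.** The unadjusted 95% half-width is 1.96 × 2.5 × √(2/1500) = 1.96 × 2.5 × 0.0365 = 0.179. Regression on the baseline score multiplies it by √(1 − ρ²).
- ρ = 0.20: 0.179 × 0.980 = 0.175 (2% narrower)
- ρ = 0.44: 0.179 × 0.898 = 0.161 (10% narrower)

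The percentages do not depend on the number of patients.

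**Step 3: carry-over of a chance baseline difference.** The shift in the QALY difference is the slope of QALYs on baseline utility times the baseline difference. Slope × baseline SD equals ρ × QALY SD, so the 95% range of the shift is ρ × 0.179.
- ρ = 0.20: ±0.036
- ρ = 0.44: ±0.079 (±0.082 at QALY SD 2.6)

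Working directly from the smallest simulated slope (2.0 QALYs per unit of utility) and SD 0.20, the chance imbalance is 1.96 × 0.20 × 0.0365 = 0.0143, and the shift is ±0.029. The range is therefore about ±0.03 to ±0.08, or 15% to 40% of 0.205 (0.03/0.205 and 0.08/0.205).

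**Step 4: power.** At a true difference of 0.205, power is Φ(0.205/[2.5 × 0.0365 × √(1 − ρ²)] − 1.96): 61.2% unadjusted, 63.0% at ρ = 0.2, 65.3% at 0.3 and 68.8% at 0.4.

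**Sensitivity.** A second simulation held each patient's utility constant over follow-up with SD 0.25. It gave QALY SD 3.0 and ρ = 0.22, 0.37 and 0.51 for baseline-to-later correlations of 0.3, 0.5 and 0.7. Adjustment then narrows the interval by 2%, 7% and 14%. The last of these goes with a carry-over of ±0.11. That is a strong assumption about persistence, and I do not rest the point on it.

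**The case against.** The strongest reply is that nothing in the article is wrong. The reporting sentence sets a format, and a regression-adjusted mean difference would satisfy it. The choice of covariates for an economic endpoint commonly sits in a statistical or health-economic analysis plan, which is not shown and may already specify adjustment. This stands in part, and it is why the point is minor. It does not remove the point, because the article is not silent. It describes how QALYs are built ("will be calculated in the same way, using results from the EQ-5D annual questionnaires") and how they are compared, and following that description gives an unadjusted difference.

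A reader might go further and infer any of the following, which the documents do not support.

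- **That the result would be biased.** Under randomisation the unadjusted difference is unbiased. Its standard error already allows for chance imbalance, and so do acceptability curves built from it. What remains is lost precision and, given the imbalance actually observed, a shift that could have been corrected.
- **That the plan commits to raw comparisons of all quality-of-life scores.** The article never says raw or unadjusted. The reporting sentence belongs to the cost-effectiveness paragraph, and no analysis specific to SF-36 or Rose is fixed.
- **That the main results are exposed.** The primary outcome is death and the main economic outcome is life years. Neither has a baseline score.
- **That the carry-over reaches half the expected gain, or that adjustment adds some 12 points of power.** The first pairs a high slope with a baseline SD of 0.30, outside the first simulation's SDs. The second needs ρ = 0.5, above that simulation's maximum of 0.44.

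**Conclusion.** The point holds in a limited form. As described, incremental QALYs are most naturally an unadjusted difference, although the baseline EQ-5D is collected. The cost is a 95% interval 2% to 10% wider than an adjusted analysis would give, and a chance carry-over of about ±0.03 to ±0.08 QALYs beside an expected gain of roughly 0.2. The gain in power is about 2 to 8 points for ρ of 0.2 to 0.4.

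Every SD, correlation, slope and utility here is an assumption; only the mortality rates and the 1500 per arm come from the article. If the second internal mammary artery also improved utility, the expected gain would be larger and the carry-over proportionately smaller. The matter is a minor improvement in efficiency and clarity, not an error that threatens a conclusion.

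**What to change.** In Analyses of cost-effectiveness and quality of life data, add that incremental QALYs will be estimated by regression of each patient's QALYs on arm and baseline EQ-5D. State that this adjusted difference is the one used in the cost per QALY, net benefit and acceptability curves, with the arm means kept as descriptive. Include the baseline score in the multiple imputation already planned.

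Specify that the baseline score is taken before the allocation is known. Table 2 says only pre-operative, and the randomisation section allows up to six weeks between randomisation and surgery, so a pre-operative score could follow the allocation.

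The cost is a sentence or two and slightly more analysis, with no new data, patients or staff. The small drawback is that missing baseline scores must be imputed. If an unseen analysis plan already specifies this, a cross-reference is enough.

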#### Sub-group analyses

i. Diabetic vs nondiabetic

ii. Age > 70 years vs age <70 years

iii. On-pump vs off-pump

iv. Radial vs vein grafts

v. Number of grafts

vi. Left ventricular failure

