**Methods/Design:**

Twenty centres in the UK, Australia, Poland and Brazil are planning to randomise 3000 coronary artery bypass graft surgery patients to single or bilateral internal mammary artery grafting. Supplemental grafts may be either saphenous vein or radial artery. Coronary artery bypass grafting can be performed as an on-pump or off-pump procedure. The primary outcome is survival at 10 years and secondary end-points include clinical events, quality of life and cost effectiveness. The effect of age, left ventricular function, diabetes, number of grafts, vein grafts and off-pump surgery are pre-specified subgroups.

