### Randomisation and enrolment process

All patients requiring CABG should be considered for entry into the study. Centres should keep a screening log and record if the patient is entered into the study and if not the reason why not. Patients who meet the eligibility criteria and give written informed consent should be randomised.

Randomisation will be performed by telephone contact with the trial co-ordinating centre (the Clinical Trials and Evaluation Unit (CTEU) based at the Royal Brompton Hospital in London). The randomisation service will be available 09:00–17:00 (UK time). Centres will be asked for a few simple details about the patient including initials, date of birth and eligibility criteria. The caller will be given the procedure allocation (SIMA or BIMA) and a fax will be sent to the centre confirming this.

Eligible patients will be randomised in equal proportions between the two surgical strategies SIMA or BIMA. The allocated procedure will be performed by a trial nominated surgeon who has been approved by the Trial Steering Committee as being sufficiently experienced (ie. performed >50 BIMA procedures).

Randomisation will be stratified by centre with specific tables using block allocation to provide treatment distribution in equal proportions. The block size will itself be subject to random variation.

To reduce the possibility of outcome measure events occurring after randomisation and before revascularisation, surgery should be performed within 6 weeks of randomisation.

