### Surgical procedure

It is left to the individual centres to decide the optimal anaesthetic technique and method of myocardial protection for each patient. As there is a consistent mortality of around 2.5% for CABG across most UK centres this suggests that minor differences in anaesthetic technique and methods of myocardial protection do not have a major influence on perioperative mortality. Surgical details will be recorded in the case report form (CRF). The only requirement is that the surgeon follows the randomisation allocation given for the patient (ie. SIMA or BIMA).

Surgery can be performed with cardiopulmonary bypass or as an off-pump procedure according to the experience of the surgeon.

The following surgical procedures should be applied depending on the allocation to SIMA or BIMA:-

**SIMA **– standard operation using SIMA to LAD plus supplemental vein or radial artery graft

**BIMA **– both IMA placed to left sided coronary arteries with supplemental vein or radial artery. The IMA grafts can be used as composite grafts to each other, as long as one remains *in situ*.

Possible combinations include

• LIMA to OM and RIMA to LAD

• LIMA to LAD and RIMA to OM (via transverse sinus)

• LIMA to LAD and RIMA as composite graft to OM

Some typical examples of SIMA and BIMA grafts are shown in Figure 1.

Please note that anastomosis of an IMA graft to the right coronary artery is an exclusion criteria (because of evidence of inferior long-term patency).

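### Three of the six pre-specified subgroups are features of the operation settled after allocation is known; for radial versus vein, membership depends on the arm, and for pump use and graft number nothing rules this out

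*Protocol article*

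**What the plan says.** The Sub-group analyses section of the protocol article gives six bare headings. Three describe the patient: diabetes, age and left ventricular failure. The other three describe the operation: "iii. On-pump vs off-pump", "iv. Radial vs vein grafts" and "v. Number of grafts". The abstract draws no line between the two kinds: "The effect of age, left ventricular function, diabetes, number of grafts, vein grafts and off-pump surgery are pre-specified subgroups".

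On timing, Randomisation and enrolment process says of the call: "Centres will be asked for a few simple details about the patient including initials, date of birth and eligibility criteria". It continues: "The caller will be given the procedure allocation (SIMA or BIMA) and a fax will be sent to the centre confirming this". Surgery is to follow within 6 weeks. Randomisation is stratified by centre, and no operative factor is named as a stratifier. In Table 1 (Follow-up), operation details are ticked only in the intra-operative column.

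On the operation, the Surgical procedure section fixes only the SIMA or BIMA allocation. For pump use it says: "Surgery can be performed with cardiopulmonary bypass or as an off-pump procedure according to the experience of the surgeon". The SIMA operation is one mammary graft to the LAD together with a vein or radial graft. The BIMA operation puts both mammary arteries on left-sided vessels, and the Trial design section makes supplemental grafts conditional on need. The only exclusion by graft number is a single graft.

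**The concern.** A subgroup comparison keeps the protection of randomisation when membership is fixed before allocation or cannot be influenced by it. As written, the three operative subgroups meet neither condition: an unblinded surgeon settles them once the arm is known. If the arm changes who enters a category, SIMA and BIMA patients within it can differ in coronary disease and risk, and a difference between subgroups may reflect selection rather than treatment. The intention-to-treat rule in Type of analyses protects the overall comparison, but not strata formed after allocation. At stake is the reading of any apparent interaction, for example that BIMA helps only in patients with one type of supplemental conduit.

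**Working it through.** **1. The plan's own figure.** Trial size gives 2928 patients for 25% versus 20% 10-year mortality, 90% power and 5% alpha. With two-sided alpha and pooled variance, n per arm = [1.960 x sqrt(2 x 0.225 x 0.775) + 1.282 x sqrt(0.25 x 0.75 + 0.20 x 0.80)]^2 / 0.05^2 = 1464, or 2928 in total. The figure reproduces and this point does not change it. It is used only to set the yardstick: the trial is sized for a 5-point difference.

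**2. When each subgroup variable is fixed.**

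| Subgroup | Nature | Fixed before allocation? | Dependence on arm |
|---|---|---|---|
| Diabetes, age, left ventricular failure | patient | yes | none |
| Radial vs vein | operation | not stated | follows from the two operations |
| Pump use | operation | not stated | possible, not shown |
| Number of grafts | operation | not stated | possible, not shown |

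**3. Radial versus vein.** Take a patient who needs two grafts, both to left-sided vessels. This patient is eligible, because only single-graft patients are excluded. Under SIMA the second vessel takes a vein or radial graft, so the patient falls in one of the two categories. Under BIMA the second mammary artery can serve that vessel, no supplement may be needed, and the patient falls in neither. The same patient is counted in one arm and not in the other.

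**4. Size, on assumed figures.** The documents give no conduit frequencies by arm or risk, so all inputs here are assumptions. Suppose treatment has no effect, half the patients are low risk and half high risk, and mean mortality is 25%. Let rL and rH be the proportions receiving a radial graft in the low- and high-risk halves of an arm, and mL and mH their mortality. Then

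mortality in the radial subgroup of that arm = (rL x mL + rH x mH) / (rL + rH),

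and the vein subgroup uses 1 - r in place of r. False BIMA-minus-SIMA differences, in percentage points, are shown first for mortality 20%/30% and then for 15%/35%:

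| Radial use, SIMA (low/high) | Radial use, BIMA (low/high) | Radial subgroup | Vein subgroup | Radial minus vein |
|---|---|---|---|---|
| 40%/20% | 40%/20% | 0; 0 | 0; 0 | 0; 0 |
| 40%/20% | 20%/20% | +1.7; +3.3 | -0.7; -1.4 | +2.4; +4.8 |
| 40%/10% | 15%/15% | +3.0; +6.0 | -1.0; -2.0 | +4.0; +8.0 |
| 30%/30% | 20%/10% | -1.7; -3.3 | +0.3; +0.6 | -2.0; -3.9 |

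Worked example (third row, 15%/35%): SIMA = (0.40 x 0.15 + 0.10 x 0.35) / 0.50 = 0.19; BIMA = (0.15 x 0.15 + 0.15 x 0.35) / 0.30 = 0.25; difference +6.0 points.

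The first row matters as much as the others: if conduit choice is independent of arm within risk groups, the error is zero even though the variable is settled after allocation. The calculation counts everyone without a radial graft as vein. The radial column does not depend on that simplification; the vein and last columns do.

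**5. Losing two-graft BIMA patients is not by itself a false interaction.** Assume 20% of patients need two grafts with 15% mortality, and the rest have 27.5%, so that 0.2 x 0.15 + 0.8 x 0.275 = 0.25. Suppose all two-graft BIMA patients need no supplement. Removing them from the BIMA arm alone gives a false risk ratio of 0.275 / 0.25 = 1.10. If conduit choice is unrelated to graft number, both strata carry the same 1.10 and the ratio of ratios is 1. A false interaction needs the further step in item 4, where conduit choice is related to risk differently in the two arms.

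**The case against.** A reader might infer that allocation partly determines all three operative factors, so that none of the three subgroups gives a randomised comparison. The article does not support that. Pump use is said to follow the surgeon's experience; a factor that mainly tracks surgeon or centre would stay largely balanced, because randomisation is stratified by centre. Off-pump patients are named in the inclusion criterion, so intended pump use may be known at entry. Graft number is driven largely by disease extent, and the single-graft exclusion means some count is judged beforehand. The Background mentions the greater difficulty of BIMA as a perception and puts the added time at about 30 minutes; it does not say that pump use or graft number changes as a result. These points stand, and they limit the finding for those two subgroups to lack of protection.

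It can also be said that the details listed for the call are introduced as examples, that the headings do not say planned or performed, and that such definitions commonly sit in a full protocol or analysis plan that is not shown. This is fair, and it is why the point is not that a definition is missing. What remains is that the article names the three on equal terms with baseline subgroups, and that a later analysis plan cannot recover an intended conduit that was not recorded before allocation.

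Finally, how these results will be presented is not stated, so a claim that a false interaction would be reported as established goes beyond the text.

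**Conclusion.** The point holds in limited form. For radial versus vein, the arm affects membership by the definition of the two operations, and the within-subgroup comparison is not a randomised one. For pump use and number of grafts, the comparisons are open to post-randomisation selection, but bias is not shown. The primary comparison and the sample size are untouched.

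No size can be taken from the documents. On the assumed inputs the false difference in the radial subgroup runs from about -3 to +6 points, in either direction and at worst as large as the 5-point design effect. It is zero if conduit choice is independent of arm within risk groups. The range shows what is possible; it is not an estimate for this trial.

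**What to change.** At the randomisation call, before the allocation is released, record the surgeon's intended pump use, intended supplemental conduit and intended number of grafts (or number of diseased vessels). Define subgroups iii to v by these answers. Report analyses by the operation performed, and any for patients without a recorded plan, as non-randomised and descriptive.

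The cost is three further items on an existing call. It is not nil: co-ordinators enrol patients and surgery may follow up to 6 weeks later, so the surgeon's plan has to be available at the time of the call. Operations that depart from the plan will dilute the subgroup contrast. For patients already randomised without a recorded plan, only the labelling can change.

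Separately, the age subgroup as printed leaves patients aged exactly 70 in neither group. That is a minor boundary correction which can be made in the same edit; it lends no support to this point.
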